### Description of the smart phone app

1) Making appointments: the app will automatically push immunization information to each village doctor in the intervention arm. Once a child has established his/her immunization card, township doctors will enter the child’s general information and immunization information into the child EPI information system (computer platform). The system will automatically assign this information to corresponding village doctors and push child’s immunization information and scheduled vaccine dates to village doctors’ smart phone through this app (Figure 
3).

**Figure 3 F3:**
[figure not shown]
**Screenshot of the EPI app.** Legend: first screenshot shows the general function modules of EPI app. Second screenshot shows the list of scheduled vaccination appointments. The last screenshot shows the health education information.

2) Record: on the scheduled vaccine date, when a child comes to the village clinic and gets his/her vaccine, the village doctor will use the app to record a child’s immunization status (name of the vaccine, date, batch number, manufacturer, vaccine site and whether it is a free shot or not). The updated immunization information of a child will be updated to the local immunization management system automatically through the 3G wireless network.

3) Tracking: a list with the names of all children who missed their immunization appointment three times will be sent to village doctors in their catchment area. The name list also includes contact information (family phone number, cell phone number and address) of children’s caregivers. The village doctor will use this list to call children’s caregivers or drop by children’s homes to remind them about immunization.

4) Health education: program managers will tailor health information related to immunization such as the abnormal reactions, key knowledge and skills of intradermal and subcutaneous injections and send this to village doctors through this app. In this way, village doctors will learn knowledge about immunization at any time or any place.

#### Co-interventions and contamination

There are no known co-occurring health programs in this community that could potentially alter the outcomes. In addition, no other child health trials have ever been conducted in this community. To reduce the risk of contamination, we will assign each village doctor in the intervention arm a unique ID and password to log in the EPI app to avoid smart phone share between village doctors in the intervention arm and control arm.

### Control

1) Making appointments: when caregivers take their children to village clinics in control arm to receive vaccines, village doctors will schedule the next appointment for vaccination with caregivers. After that, when they manually update children’s information on the child EPI information system, the system will also generate a list on paper including the dates when children should have subsequent vaccinations. Then village doctors will bring this list as a reference for further appointments.

2) Record: on the scheduled vaccine date, when a child comes to the village clinic and gets his/her vaccine, the village doctor will record this child’s immunization status (name of the vaccine, date, batch number, manufacturer, vaccine site and whether it is a free shot or not) on paper. Then they will go to township hospitals to manually input children’s immunization information into the child EPI information system once a month.

3) Tracking: a name list with all overdue children who missed their immunization appointment will be manually generated from township hospitals monthly and then township hospital doctors will inform the village doctors by telephone calls.

4) Health education: village doctors will be trained at the township hospital during monthly regular meetings.

### Randomization

The unit of randomization will be the cluster, defined by the administrative boundary for each village. Randomization will be performed after the baseline household survey. A statistician outside the research team will be responsible for the randomization.

A short pre-randomization survey was conducted to explore the general characteristics of village doctors who provided immunization services in their catchment areas, as well as their mobile phone use preferences. There are 59 village doctors that provide immunization services in our study area.

For villages (n = 18) that have more than one village doctor who manages immunization, we will only include the youngest village doctor, because we assume younger doctors have better mobile phone use skills and can potentially increase the uptake and sustainability of the intervention. Four villages will be excluded because of the small number of children (<7 children aged 12–23 months) in these villages. One village will be randomly excluded because we use a paired design. In total, 36 villages (18 pairs) will be included for randomization.

Package of blockTools in R
[17] will be used for matching and random allocation, for multiple continuous variables were allowed. We will use the number of children younger than 1 year managed by the village doctor in charge of vaccination injection, age of the youngest village doctor for immunization in village, and the population density (population/area in each village) for pair matching.

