### Sample size and study population

A. Sample size calculation

Base on a survey conducted in early 2013 in Xuanhan County, Sichuang Province, the coverage of the five key vaccines is 41.35%. We expect that the five-vaccination coverage in intervention group will rise from 41.35% to 65%.With level of confidence of 95%, power of 80%, the coefficient of variation in outcome between clusters within matched pairs (Km) as 0.25
[18], we estimate that 7 participants from each cluster of 18 pairs of clusters will be sufficient to detect the difference in two groups.

B. Intervention target will be village doctor in charge of immunization

Inclusion criteria

a. Village doctors who are in charge of immunization (both management and injection)

b. If there are several village doctors available, we will choose the youngest one and with the assistant practicing license for clinical doctors

Exclusion criteria

a. Refuse to participate

b. The estimated number of children aged one to two years in village is less than 7. The estimated number is calculated as the number of children reported multiplied by 75% (the average percentage of children staying in the village) and 90% (the expected rate of contacted primary caregivers who agree and complete the survey).

C. The survey target will be caregivers of children aged 12–23 months. Children aged over 1 year are supposed to complete the five vaccinations required by national EPI program. Therefore, caregivers of children aged 12–23 month old are our survey target in both the baseline and endline survey.

Inclusion criteria

a. Living in Xuanhan County

b. Receiving immunization service in Xuanhan County

c. Having a child aged 12 to 23 months; if there is more than one child aged 12 to 23 months, only include the youngest one

d. Being a caregiver of the selected child

Exclusion criteria

a. Refuse to participate.

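### Neither the pair matching nor the stated covariate adjustment uses village baseline coverage or township, although the sample size has little reserve for within-pair variation

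*Protocol article*

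**What the plan says.** The Randomization section lists the matching variables in full: "We will use the number of children younger than 1 year managed by the village doctor in charge of vaccination injection", then "age of the youngest village doctor for immunization in village, and the population density (population/area in each village) for pair matching". Township is not among them, and no stratification is described. The only reason given is that the software accepts several continuous variables. The same section states "Randomization will be performed after the baseline household survey". That survey covers caregivers of children aged 12–23 months, as at endline (Sample size and study population), and is the source of the coverage outcome (Outcome measurement).

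The trial runs in two townships, one with 31 villages and one with 15 (Study area). In the control arm the list of overdue children "will be manually generated from township hospitals monthly"; township doctors then telephone the village doctors, and training takes place at the township hospital (Control). In the app arm, township doctors enter each child's data and are the first line of support (Description of the smart phone app; Training).

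The sample size takes "the coefficient of variation in outcome between clusters within matched pairs (Km) as 0.25" and concludes "we estimate that 7 participants from each cluster of 18 pairs of clusters will be sufficient to detect the difference in two groups". The village-level analysis is a paired t test or a non-parametric test on transformed coverage. A random-effects logistic model adds individual-level socioeconomic covariates (Data management and analysis).

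**The concern.** Matching and covariate adjustment gain precision only to the extent that the variables used predict the outcome. For village coverage at endline, the obvious candidates are coverage in the same village at baseline and the township whose hospital organises follow-up. Both are known before allocation and neither is used. The protocol does not show that the three chosen variables predict coverage.

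With 36 villages, chance differences in starting coverage or township mix between the arms can be appreciable. Pairs may also cross townships, so that any township difference enters the within-pair contrast. What is at stake is precision and chance imbalance in a trial whose power rests on the assumed Km of 0.25.

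**Working it through.** **Inputs.** From the Sample size section: control coverage p0 = 0.4135, intervention coverage p1 = 0.65, m = 7 children per village, 18 pairs, Km = 0.25, 95% confidence and 80% power. A two-sided test is assumed, as the sidedness is not stated. From Study area: villages split 31:15. All calculations are on the untransformed proportion scale.

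**1. The plan's own figure.** The pair-matched cluster formula is

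pairs = 2 + (z0.975 + z0.80)² × V / (p1 − p0)², with V = p0(1−p0)/m + p1(1−p1)/m + Km²(p0² + p1²).

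- Sampling part: 0.2425/7 + 0.2275/7 = 0.0671.
- Between-village part: 0.0625 × 0.5935 = 0.0371.
- V = 0.1042, (p1 − p0)² = 0.0559, (z0.975 + z0.80)² = 7.849.
- Pairs = 2 + 7.849 × 0.1042 / 0.0559 = 16.6, so 17 against 18 planned.

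Solved for m at 18 pairs, the formula gives 6.11, which rounds up to the stated 7. The sample size follows from its inputs.

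**2. Reserve.** Setting pairs = 18 and m = 7 and solving for Km gives 0.281. Power from the noncentral t with 17 degrees of freedom, noncentrality (p1 − p0)/√(V/18):

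| Km | Pairs needed | Power, 17 df |
|---|---|---|
| 0.20 | 15 | 88% |
| 0.25 | 17 | 83% |
| 0.30 | 19 | 78% |
| 0.35 | 22 | 72% |
| 0.40 | 25 | 65% |

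By the t calculation, too, power reaches 80% at Km of about 0.28. A plain normal approximation, without the small-sample correction, would put that limit at about 0.32.

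**3. Township, under assumptions.** The documents give no coverage by township. Assume a within-township coefficient of variation (CV) of 0.25, pairing that ignores township, and shares of 15/46 and 31/46. A gap d adds variance w(1−w)d² with w(1−w) = 0.326 × 0.674 = 0.220. The effective CV is then √(0.25² + 0.220 d²/0.4135²):

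- d = 10 points: 0.27, power 81%
- d = 15 points: 0.30, power 77%
- d = 20 points: 0.34, power 73%

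This lets the gap scale with coverage in the intervention arm, as a common CV implies. If the gap is the same number of points in both arms, 2 × 0.220 d² is added to V instead. The equivalent CVs are then about 0.26, 0.28 and 0.30, with power of 82%, 80% and 77%. Under blind pairing the expected share of cross-township pairs is 2 × 31 × 15 / (46 × 45) = 45%. Matching on density may lower it.

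**4. What baseline coverage can contribute.** With 7 children at baseline, the reliability R of village coverage is vb/(vb + vw), where vb = (CV × p0)² and vw = [p0(1−p0) − vb]/7.

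- CV 0.25: 0.0107/(0.0107 + 0.0331) = 0.24.
- CV 0.40: 0.0274/(0.0274 + 0.0307) = 0.47.

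In the best case true village coverage is stable until endline, and the residual CV is CV × √(1−R). That takes 0.25 to 0.217 (power 83.4% to 86.5%) and 0.40 to 0.291 (65% to 79%). The gain is small at the planned CV and larger where the assumption fails.

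**5. Cost of uninformative matching.** At CV 0.25, power is 83.4% with 17 degrees of freedom and 85.5% with 34, a difference of about 2 points.

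**The case against.** The strongest reply is that nothing here is an error. Randomization within pairs is unbiased whichever variables are used, the sample size reproduces, and the choice of matching variables is partly judgement. The chosen ones are not arbitrary: infant count reflects workload, and the protocol itself links doctor age to phone skill and uptake. All of this stands.

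A reader might infer from the power table that this matching set costs the trial its 80% power. The documents do not support that. The table shows sensitivity to Km, as in any matched cluster trial. Nothing in the protocol shows that the achieved Km will exceed 0.25, and with a 10-point township gap the design still holds. Nor does pairing waste much by halving the degrees of freedom, since the cost is about 2 points.

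A reader might also think that matching on baseline coverage would largely solve the problem. At the planned CV its reliability is only about 0.24.

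Three further replies have partial force. The Design section speaks of comparing outcomes between baseline and endline, but the analysis section names no baseline-adjusted test, so this does not secure the adjustment. Covariates are often left to an analysis plan; here, however, the article states both the matching set and the type of covariate, and the listed ones are all individual-level, though given as examples. Finally, the Training section reports in the past tense that intervention doctors were trained in January 2014, while Randomization is written in the future tense. Allocation may already have been made, and re-matching would then be impossible.

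**Conclusion.** The point holds as a matter of efficiency and chance imbalance, not of validity. The two most plausible village-level predictors of the outcome are available before allocation and appear in neither the matching nor the stated adjustment. The sample size tolerates Km only up to about 0.28 against the assumed 0.25.

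The size of any loss cannot be derived from the protocol, which gives neither coverage by township nor any correlation between the matching variables and coverage. The township range of about 0.27 to 0.34 rests on assumed gaps of 10 to 20 points, a within-township CV of 0.25, a 31:15 split among the included villages and pairing blind to township. It is smaller if the gap does not grow with coverage. This is a cheap improvement worth making; the trial does not depend on it.

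**What to change.** Prespecify village baseline five-vaccine coverage and township as covariates in the primary analysis. For example, regress the 18 within-pair endline differences on the within-pair differences in baseline coverage and in township, with the intercept as the intervention effect, and add both variables to the random-effects logistic model. If every pair lies within one township, the township difference is zero throughout and that term drops out of the paired regression.

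If allocation has not yet been run, also form the pairs within township. Township is known without error. One pair may have to cross if the included villages do not divide evenly.

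No new data, villages or children are needed. The cost is one or two degrees of freedom: if both covariates proved useless at Km 0.25, moving from 17 to 15 degrees of freedom would lower power from 83.4% to 82.7%. The expected gain from baseline coverage is modest at the planned CV, for the reliability reason shown in the working.

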### Sample size and study population

A. Sample size calculation

Base on a survey conducted in early 2013 in Xuanhan County, Sichuang Province, the coverage of the five key vaccines is 41.35%. We expect that the five-vaccination coverage in intervention group will rise from 41.35% to 65%.With level of confidence of 95%, power of 80%, the coefficient of variation in outcome between clusters within matched pairs (Km) as 0.25
[18], we estimate that 7 participants from each cluster of 18 pairs of clusters will be sufficient to detect the difference in two groups.

B. Intervention target will be village doctor in charge of immunization

Inclusion criteria

a. Village doctors who are in charge of immunization (both management and injection)

b. If there are several village doctors available, we will choose the youngest one and with the assistant practicing license for clinical doctors

Exclusion criteria

a. Refuse to participate

b. The estimated number of children aged one to two years in village is less than 7. The estimated number is calculated as the number of children reported multiplied by 75% (the average percentage of children staying in the village) and 90% (the expected rate of contacted primary caregivers who agree and complete the survey).

C. The survey target will be caregivers of children aged 12–23 months. Children aged over 1 year are supposed to complete the five vaccinations required by national EPI program. Therefore, caregivers of children aged 12–23 month old are our survey target in both the baseline and endline survey.

Inclusion criteria

a. Living in Xuanhan County

b. Receiving immunization service in Xuanhan County

c. Having a child aged 12 to 23 months; if there is more than one child aged 12 to 23 months, only include the youngest one

d. Being a caregiver of the selected child

Exclusion criteria

a. Refuse to participate.

### Outcome measurement

The primary outcome is five-vaccine immunization coverage and the secondary outcome is immunization coverage for Bacillus Chalmette Guerin (BCG), Oral Poliomyelitis Vaccine (OPV), Diphtheria Pertussis Tetanus Combined Vaccine (DTP), Measles Vaccine (MV), Hepatitis B Vaccine (HBV), Hib vaccine, Rotavirus vaccine and Pneumococcal conjugate vaccine (PCV) vaccine (Additional file
1: Table S2).Immunization coverage will be collected by the immunization module (IM) of the household survey. The immunization card will be collected for every participant, and injection record including dosage and date will be recorded with *Goodata*, a smart phone app for data collection. The demographic information such as education level, ethnicity, gravidity, parity, type of Hukou, source of family income will also be collected by the household and identification module (HH and ID) in household survey, as they are factors that may potentially influence immunization.

### Multidimensional evaluation of smart phone app (EPI)

#### Heuristic evaluation

A heuristic evaluation is an informal usability evaluation technique to evaluate whether user interface elements of a system adhere to a set of usability principles known as heuristics
[19]. The purpose of the heuristic evaluation method is to identify any serious usability problems that users might encounter and to recommend improvements to the design before implementing the system. By evaluating the interface in the developmental phase, design problems may be identified and corrected earlier, thus reducing potential usability errors
[20].

Three experts who have experience in developing health information systems will be invited to conduct the heuristic evaluation. To make sure all the experts will receive the same guidance, materials including the user manual of EPI app, introduction of heuristic evaluation and heuristic evaluation form will be provided to them before evaluation starts. Research staff will make sure that the experts understand the procedure of evaluation and ask the experts to start using all four function modules of the app.

Violations are defined as problems that could potentially interfere with end user’s ability to interact effectively with the app
[21]. After finishing with all function modules of the app, experts will fill out the heuristic evaluation form. During evaluation sessions, experts are encouraged to “think aloud”. Research staff will use a video camera to record the heuristic evaluation and take field notes. The time for completing each task and number of errors will also be recorded.

#### Usability test

Usability testing is a way of ensuring that apps are adapted to users and their tasks
[22]. Usability testing involves measuring the performance of end users doing typical task case scenarios
[22,23]. The goal of this fundamental step is to obtain objective performance data to assess an app in terms of usability goals: accuracy and acceptability. Accuracy will be measured by logging the time spent on completing each task and number of errors. Acceptability is defined as the extent of uptake of this app and will be assessed using users’ perception of ease of use and usefulness scale (PEUU)
[24], which will be translated and adapted into Chinese context before use.

About 10–15 village doctors will be recruited for usability testing. The inclusion criteria for village doctors are: 1) in charge of immunization of children in his/her catchment area; 2) able to use a smart phone and apps; 3) do not receive any intervention in our study. In addition, we will exclude those who refuse to participate. Village doctors who meet our inclusion criteria will be invited to participate. After obtaining their informed consent, short training will be conducted to introduce how to use the smart phone and app as well as the basic function of app, usability testing, case scenarios and the PEUU scale assessment. Then, village doctors will be asked to use the app to perform case scenarios. Research staff will observe the whole process and record the time for completing each task and number of errors. Meanwhile, during evaluation sessions, village doctors are encouraged to “think aloud” on problems they encountered or experiences while using. After obtaining their consent, research staff will use video cameras to record the village doctors to perform case scenarios and take field notes. After completion of case scenarios, village doctors will fill out the PEUU scale and be encouraged to be as specific as possible.

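### The usability-test eligibility rule leaves control-arm doctors open to being trained on the app; it should be limited to doctors outside the 36 randomized villages

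*Protocol article*

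**What the plan says.** The Usability test section of the protocol article gives the size of the exercise: "About 10–15 village doctors will be recruited for usability testing". It sets three inclusion criteria. The doctor must be "in charge of immunization of children in his/her catchment area", must be "able to use a smart phone and apps", and must be one of those who "do not receive any intervention in our study". The only exclusion is refusal: "In addition, we will exclude those who refuse to participate".

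After consent, "short training will be conducted to introduce how to use the smart phone and app". Participants then carry out case scenarios in the app while being observed and, if they consent, filmed. They finish by completing a scale on its ease of use and usefulness.

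Under Design, the village was made the unit of randomization because one doctor might share the app with another. Under Co-interventions and contamination, one measure is given: "To reduce the risk of contamination, we will assign each village doctor in the intervention arm a unique ID and password". Its stated purpose is to prevent phone sharing between arms. The Control section describes usual practice: paper records, a printed list of due dates, monthly overdue lists from the township hospital, and monthly training meetings.

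**The concern.** Control-arm doctors manage immunization in the usual way, so they receive no intervention and satisfy the third criterion as worded. They also satisfy the first. Only the second, ability to use a smart phone and apps, could remove some of them. The criterion therefore separates doctors by whether they are in the intervention arm, not by whether they are in the trial.

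The same wording admits doctors who were not selected in villages with more than one immunization doctor, in either arm.

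A control doctor who is recruited would be shown the app, would practise with it and would receive attention from the research team. The comparator would then no longer be purely usual practice. The login measure cannot prevent this, because the exposure would come from the study team and not from a colleague's phone. In a trial that chose village randomization to limit contamination, its own sub-study should not leave this route open.

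**Working it through.** **Who qualifies.** Each criterion applied to each group of doctors:

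| Group | In charge of immunization | Can use smart phone and apps | Receives no intervention | Barred elsewhere in the article? |
|---|---|---|---|---|
| Intervention-arm doctors (18) | yes | some or all | no | excluded by criterion 3 |
| Control-arm doctors (18) | yes | some or all | yes | no |
| Non-selected doctors in trial villages | yes | some or all | yes, as worded | no |
| Doctors outside the 36 villages | yes | some or all | yes | no |

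**How many control doctors could be exposed.** Inputs: 59 village doctors provide immunization in the study area (Randomization); 18 villages per arm, with one trial doctor each (Abstract, Randomization); 497 villages in the county (Study area); 10–15 recruits (Usability test). The recruitment area is not stated, so three cases are shown. All assume that every doctor passes criterion 2.

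- *Random draw from the study area.* Doctors outside the intervention arm: 59 − 18 = 41, of whom 18 are control-arm. Expected control doctors: 10 × 18/41 = 4.4 and 15 × 18/41 = 6.6, or 24% to 37% of the control arm.
- *Random draw from the whole county,* assuming one eligible doctor per village: 497 − 18 = 479. Expected control doctors: 10 × 18/479 = 0.4 and 15 × 18/479 = 0.6.
- *All recruits from the control arm* (ceiling): 10/18 = 56% and 15/18 = 83%.

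**What dilution could cost.** First, the plan's own sample size. The inputs from Sample size and study population are p0 = 0.4135, p1 = 0.65, Km = 0.25, 80% power and 18 pairs; a two-sided 5% level is assumed. The matched-pair formula is

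c = 2 + (1.96 + 0.84)² × V/(p1 − p0)², with V = [p0(1 − p0) + p1(1 − p1)]/m + Km²(p0² + p1²).

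At m = 7, V = 0.0671 + 0.0371 = 0.1042 and c = 16.6, so 17 pairs suffice. With c = 18 the required m is 6.11, rounded up to 7. The stated 7 per cluster reproduces. Power at 18 pairs of 7 is Φ(√[16 × 0.2365²/0.1042] − 1.96) = Φ(0.97) = 83%.

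Now let n control villages be exposed and let each gain a share s of the app's effect. The control rate becomes p0 + (p1 − p0) × s × n/18, and power is recalculated with the same formula. The documents give no value for s, so it is an assumption.

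| Control villages exposed | s = 25% | s = 50% | s = 100% |
|---|---|---|---|
| 0 | 83% | 83% | 83% |
| 0.6 (county-wide draw) | 83% | 82% | 81% |
| 4 | 79% | 73% | 61% |
| 7 | 75% | 64% | 41% |

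The right-hand column would need one short session to match eight months with a supplied phone, pushed schedules and missed-child lists. It is a bound and not a forecast.

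**The case against.** The strongest reply is that eligible does not mean recruited. The section names no recruitment area, the authors may have meant doctors outside the trial, and a condensed article may leave the sampling frame to a fuller protocol. That stands as a limit on certainty. It does not remove the point, because the article states its inclusion and exclusion criteria explicitly and those criteria admit the comparator arm.

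The second reply concerns size. The app works through continuing supply: a phone with paid network access, automatic schedules, on-the-spot recording and tracking lists. Usability participants are not said to keep any of these. Without an issued login, a control doctor could not use the app in practice afterwards, so the login measure does limit sustained use even though it does not prevent the training. Control doctors also already have schedules, overdue lists and monthly education. The Feasibility evaluation section is placed after usability testing, which suggests a single early session. All of this stands and points to small carry-over.

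Third, contamination of controls would most plausibly bias towards no effect. It would not be expected to create a spurious benefit, and randomization, the primary outcome and the planned analysis are unchanged.

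A reader might infer that the plan will train control doctors, that a quarter or more of the control arm will be exposed, or that power will collapse. The documents do not support these readings. The first goes beyond an eligibility rule, the second assumes recruitment only within the two townships, and the third needs a carry-over far larger than a short session makes likely.

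**Conclusion.** The point holds as a defect of wording with a real but uncertain consequence. As written, smart-phone-able control-arm doctors and non-selected doctors in trial villages may be trained on the app, and no stated safeguard covers that exposure.

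The number of control doctors affected ranges from under 1 to a ceiling of 10–15, with 4 to 7 if recruitment is a random draw within the study area. Each figure rests on an assumed recruitment area and on all doctors passing the smart-phone criterion.

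Dilution is probably modest. At an assumed 25% carry-over with 4 to 7 villages exposed, power falls from about 83% to 75–79%. This should be fixed before usability recruitment, because exposure cannot be undone and an intention-to-treat analysis keeps the exposed villages. It is not a reason to doubt the design as a whole.

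**What to change.** Change the third usability criterion to require that the doctor works outside the 36 randomized villages, for example in the villages excluded from randomization or in another township of the county. Add a sentence that no doctor from a trial village, selected or not, takes part in usability testing before endline.

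The exercise does not depend on control doctors. The excluded villages alone may be too few: the Randomization section excludes five, and if each has one or two immunization doctors they supply only about 5 to 10, before the smart-phone criterion and refusals. Some recruitment from another township is therefore likely to be needed. With 55 townships and 497 villages in the county, and an app built for that county, 10–15 suitable doctors should be available.

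The cost is one eligibility line, one added sentence and some extra travel. The sample size and analysis do not change.
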